## 7.1.2 Q1W Dosing Schedule

**Table 14. Schedule of Assessments (Q1W)**

|                                                                         | Screening         | Treatment Period           |                     |                     |                     |                     |                                              |                                             | Follow-up              |                          |
|-------------------------------------------------------------------------|-------------------|----------------------------|---------------------|---------------------|---------------------|---------------------|----------------------------------------------|---------------------------------------------|------------------------|--------------------------|
| Visit                                                                   |                   | Cycle 1                    | Cycle 2             | Cycle 3             | Cycle 4             | Cycle 5             | Cycle 6                                      | Cycle 7 +                                   | Safety FU c | Survival FU d |
| Visit days a                                                 | Days
-28 to -1 | Day 1,2,5,8,11,
15,19   | Day 1,8,15          | Day 1,8,15          | Day 1,8,15          | Day 1,8,15          | Day 1,8,15                                   | Day 1,8,15                                  |                        |                          |
| Assessment                                                       |                   |                            |                     |                     |                     |                     |                                              |                                             |                        |                          |
| Informed consent e                                           | X                 |                            |                     |                     |                     |                     |                                              |                                             |                        |                          |
| Eligibility review f                                         | X                 |                            |                     |                     |                     |                     |                                              |                                             |                        |                          |
| Medical history g                                            | X                 |                            |                     |                     |                     |                     |                                              |                                             |                        |                          |
| Demography                                                              | X                 |                            |                     |                     |                     |                     |                                              |                                             |                        |                          |
| Cancer disease and treatment history h                       | X                 |                            |                     |                     |                     |                     |                                              |                                             |                        |                          |
| Echocardiography or MUGA scan                                           | X                 |                            | X (D1) i |                     |                     |                     |                                              |                                             | X                      |                          |
| Physical examination b,j                                     | X                 | X (D1,D8,D15)              | X                   | X                   | X                   | X                   | X                                            | X                                           | X                      |                          |
| ECOG PS j                                                    | X                 | X (D1)                     | X (D1)              | X (D1)              | X (D1)              | X (D1)              | X (D1)                                       | X (D1)                                      | X                      |                          |
| Vital signs b,k,bb                                           | X                 | X                          | X                   | X                   | X                   | X                   | X                                            | X                                           | X                      |                          |
| ECG b,l                                                      | X                 | X (D1,D8,D15) l | X (D1) l | X (D1) l | X (D1) l | X (D1) l | X (D1) l                          | X (D1) l                         | X                      |                          |
| Thyroid function b,m                                         | X                 |                            | X (D1)              |                     | X (D1)              |                     | X (Cycle 6 and every other cycle thereafter) |                                             | X                      |                          |
| Pulse oximetry b,n                                           | X                 | X                          | X                   | X                   | X                   | X                   | X                                            | X                                           | X                      |                          |
| Urinalysis b,o                                               | X                 | X (D1)                     | X (D1)              | X (D1)              | X (D1)              | X (D1)              | X (D1)                                       | X (D1)                                      | X                      |                          |
| Pregnancy test b,p                                           | X                 | X (D1,D8,D15)              | X                   | X                   | X                   | X                   | X                                            | X                                           | X                      |                          |
| Local laboratory safety assessments b,q                      | X                 | X (D1,D8,D15)              | X (D1,D15)          | X (D8)              | X (D1,D15)          | X (D8)              | X (D1,D15)                                   | X q                              | X                      |                          |
| Immunology aa                                                | X                 | X (D1)                     | X (D1)              | X (D1)              | X (D1)              | X (D1)              | X (D1)                                       | X (D1)                                      | X                      |                          |
| Central laboratory assessments in the events of IRR or CRS v |                   | (X)                        | (X)                 | (X)                 | (X)                 | (X)                 | (X)                                          | (X)                                         |                        |                          |
| HBV, HCV test t                                              | X                 |                            |                     |                     |                     |                     |                                              |                                             |                        |                          |
| PK b,s                                                       |                   | X                          | X                   | X                   | X                   | X                   | X                                            | X                                           | X                      |                          |
| Immunogenicity (ADA) b,s                                     |                   | X (D1,D8,D15)              | X                   | X (D1)              | X (D1)              | X (D1)              | X (D1)                                       | X (D1)                                      | X                      |                          |
| Blood biomarkers b,s                                         |                   | X                          | X                   | X                   | X (D1,D8)           | X (D1)              |                                              |                                             | X                      |                          |
| Tumor assessment by CT/MRI u                                 | X t    |                            | X u      |                     | X u      |                     |                                              | X (Cycle 7 and every 3 rd cycle) | X u         |                          |

CONFIDENTIAL

May not be used, divulged, published, or otherwise disclosed without the consent of  
Molecular Partners AG, Schlieren, Switzerland

|                                                              | Screening         | Treatment Period         |            |            |            |            |            |             | Follow-up              |                          |
|--------------------------------------------------------------|-------------------|--------------------------|------------|------------|------------|------------|------------|-------------|------------------------|--------------------------|
| Visit                                                        |                   | Cycle 1                  | Cycle 2    | Cycle 3    | Cycle 4    | Cycle 5    | Cycle 6    | Cycle 7 +   | Safety FU c | Survival FU d |
| Visit days a                                      | Days
-28 to -1 | Day 1,2,5,8,11,
15,19 | Day 1,8,15 | Day 1,8,15 | Day 1,8,15 | Day 1,8,15 | Day 1,8,15 | Day 1,8,15  |                        |                          |
|                                                              |                   |                          |            |            |            |            |            | thereafter) |                        |                          |
| Tumor biopsy (archival) w                         | X                 |                          |            |            |            |            |            |             |                        |                          |
| Tumor biopsy (fresh), pre and on-treatment b, x   | X                 |                          | X (D8)     |            |            |            |            |             |                        |                          |
| Tumor biopsy (fresh), on PD/response (optional) y |                   | (X)                      |            |            |            |            |            |             | (X)                    |                          |
| Skin biopsy b                                     | X cc   | X (D5,D8) cc  |            |            |            |            |            |             |                        |                          |
| Adverse events                                               | X dd   | X                        | X          | X          | X          | X          | X          | X           | X                      | X cc          |
| Prior and concomitant medication                             | X                 | X                        | X          | X          | X          | X          | X          | X           | X                      |                          |
| MP0317 administration z                           |                   | X (D1,D8,D15)            | X          | X          | X          | X          | X          | X           |                        |                          |
| Survival information                                         |                   |                          |            |            |            |            |            |             |                        | X                        |

a **Visit days.** Visits are in calendar days, not business days.

b **Detailed schedule of assessments.** For assessment time points and/or allowed visit windows see Table 15 to Table 20.

c **Safety FU.** At Week 4 ( $\pm$  1 week) after the last study drug administration (Section 7.3.2). All patients should complete the safety FU period after treatment discontinuation. If the safety FU visit cannot be performed (e.g. withdrawal of consent), the last visit will be considered the safety FU visit for this patient. If a subsequent anticancer treatment is initiated during the 28-day safety FU period, the safety FU visit should be before initiation of such therapy. If this is not possible, the safety (FU) visit will be done as soon as possible after initiation of such therapy.

d **Survival FU.** Survival FU will be performed after completion of the last safety FU visit or discontinuation from the study for any reason (i.e. patient EOS). Survival status will be collected by the study site via telephone contact, clinic visits and/or consultation of the patient medical records at approximately 3 ( $\pm$  2 weeks) and 6 months ( $\pm$  2 weeks) after patient EOS, or until withdrawal of consent, patient is lost to follow-up, death or study termination by the Sponsor, whichever occurs first (Section 7.3.3).

e **Informed consent.** Must be dated and signed before any study-specific procedure is performed (Section 11.1.2).

f **Eligibility review.** All inclusion/exclusion criteria must be reviewed during screening (Sections 4.2 and 4.3).

g **Medical history.** Including clinically significant diseases, surgeries, reproductive status and medication (including over-the-counter or prescription medicines, vitamins and/or herbal supplements) taken within 28 days before the first study drug administration will be recorded (Sections 6 and 7.4.1).

h **Cancer disease and treatment history.** Includes date(s) of diagnosis, classification by origin, tissue type, grade, stage, markers and mutations if available, prior anticancer treatments and procedures (Section 7.4.2).

i **Echocardiography or MUGA scan.** Measurements should follow European Society for Cardiology Guidelines 2016 and be performed pre-dose (Section 7.4.7).

j **Physical examination and ECOG PS.** Will be collected as per institutional standard practice and assessed according to ECOG criteria (Appendix 12.1). Physical examination needs to be done before each study drug administration. Abnormalities observed at screening are recorded in the medical history eCRF. At subsequent visits (or as clinically indicated), limited, symptom-directed physical examination should be performed. New or worsened clinically significant abnormalities occurring after screening should be recorded as AEs in the eCRF (Sections 7.4.3 and 8.1).

k **Vital signs.** Assessments include body weight, height (at screening only), body temperature, respiratory rate, pulse rate and blood pressure while the patient is in a supine or seated position and before any blood draws. Assessment of blood pressure and pulse rate will be preceded by at least 5 min rest for the patient in a quiet setting without distractions (e.g. television, mobile phone) (Section 7.4.4). Measurement of body weight will be made with the patient wearing indoor daytime clothing without shoes according to institutional standard practice.

l **ECG.** For each patient, ECGs should be obtained from the same machine whenever possible. Dose-escalation part: Screening, Cycle 1 D1, D8 and D15 pre-dose. From Cycle 2 onwards at D1 pre-dose only. Safety expansion part: Screening and all cycles at D1 pre-dose (Section 7.4.6).

m **Thyroid function.** TSH, free T3, free T4 will be monitored repeatedly throughout the study to detect any potential autoimmune thyroiditis (Section 7.4.8).

CONFIDENTIAL

May not be used, divulged, published, or otherwise disclosed without the consent of  
Molecular Partners AG, Schlieren, Switzerland

- n **Pulse oximetry.** To detect presence of hypoxemia (e.g. from possible pneumonitis; Section 7.4.5).
- o **Urinalysis.** Urine dipstick at screening, on Day 1 of each cycle before study drug administration, and at safety FU visit. If positive findings are noted and are thought to be of clinical significance, detailed urinalysis will be performed at a local laboratory (Section 7.4.9).
- p **Pregnancy test.** Female patients of childbearing potential will have a serum pregnancy test at screening and a serum or urine pregnancy test before each study drug administration and at the safety FU visit (Sections 7.4.10 and 8.3).
- q **Local laboratory safety assessments.** Parameters to be evaluated are detailed in Section 7.4.11. Values based on blood samples taken up to 48 h before scheduled laboratory safety assessment will be used by the Investigator to decide if the patient is suitable for study treatment (Section 5.2.3). Laboratory safety assessments from cycle 2 onwards take place before every second drug administration.
- r **HBV, HCV test.** HBV test includes HBsAg. HCV test includes HCV antibody (if positive an HCV RNA test by PCR must be done; Section 7.4.11).
- s **PK, immunogenicity (ADA) and blood biomarkers.** PK and immunogenicity (ADA) will be assessed using serum, and blood biomarkers (to evaluate disease status, safety or predictive biomarkers) will be assessed using serum, plasma and/or fresh blood. See Sections 7.4.13, 7.4.14 and 7.4.16.3 and refer to the Laboratory Manual.
- t **Tumor assessments at screening.** If a tumor assessment (including CT scan according to RECIST v1.1) was performed within 28 days before screening it is not required to be repeated and can be used as screening assessment.
- u **Tumor assessments.** Tumor measurements will be made at screening and every 6 to 8 weeks after the start of study treatment (within 7 days before first scheduled infusion of Cycles 3, 5 and 8 then every third cycle and according to institutional standard practice) until PD, withdrawal of consent, death, or study termination, whichever occurs first. CT scans will be performed using institutional standard operating procedures. In specific cases, tumor measurements may be performed by MRI scans instead of (or in addition to) CT scans. However, the same imaging modality as used for screening should be used throughout the study (Section 7.4.15).
- v **Central laboratory assessments in the events of IRR or CRS.** Cytokines, complement factors, drug-specific IgE and tryptase will be assessed in the events of IRR or CRS (Section 7.4.12). Sample should be taken 30-40 minutes after onset of the reaction.
- w **Tumor biopsy (archival).** If an archival tumor sample is available with an associated pathology report, performed at any time prior to study entry, this should be provided. However, only tissue from core needle, punch or excisional biopsy samples will be considered for study analyses, while fine needle aspiration, brushing and lavage samples are not acceptable. For all biopsy types, at least 5 to 15 unstained good quality slides should be provided or blocks that have sufficient tissue to generate at least 15 slides. Tissue for which the pathology report specifies that the overall tumor content is low (e.g. 'sparse' or 'scant') will not be considered.
- x **Tumor biopsy (fresh), pre and on-treatment.** The biopsies should be performed as follows: a) At least 1 tumor lesion  $\geq 20$  mm amenable to percutaneous biopsy other than the target lesion(s) used to follow response as defined by RECIST v1.1. b) For cutaneous or subcutaneous lesions, tumors should be  $\geq 5$  mm in diameter amenable to biopsy by excisional or punch biopsies without unacceptable risk of a major procedural complication. c) For core needle biopsy specimens, at least 3 to 6 cores with an 18-gauge needle should be collected. d) The on-treatment tumor biopsy should be taken from the same lesion as the pre-treatment biopsy. The biopsied lesion should be large enough to take both biopsies  $\geq 1$  cm apart.
- y **Tumor biopsy (fresh), on PD/response (optional).** Patients may agree to an additional tumor biopsy, preferably taken at the time of radiographic PD or response, that will be collected at the discretion of the Investigator and only if the patient is capable of providing it at the time requested.
- z **MP0317 administration.** The MP0317 infusion solution must be administered completely and the entire infusion line flushed with 25 mL 0.9% NaCl. The infusion duration should be at least 50 min (excluding flushing) and no longer than 2 h (including flushing). Usage of a 0.2  $\mu$ m in-line filter is mandatory. It is recommended to start infusions in the morning to allow adequate time for pre-infusion assessments, infusion, post-infusion medical supervision and PK assessments (Section 5.2.2). Body weight measured at Day 1 of each treatment cycle should be used for dose calculation. If an infusion bag needs to be prepared one day prior to the Day 1 visit of the respective cycle, body weight measured at the previous visit should be used (Section 5.1.2).
- aa **Immunology.** Assess beginning of each cycle (parameters to be evaluated are detailed in Section 7.4.11).
- bb **Height.** At screening only. Measurements will be made with the patient wearing indoor daytime clothing without shoes according to institutional standard practice (Section 7.4.4).
- cc **Skin biopsy.** Pre and on-treatment skin samples will be taken from mirror areas of normal skin. They will be obtained using a 2 and a 4 mm diameter punch biopsy device to create the injury and to collect the wound healing material, respectively. Two skin biopsies will be collected during screening with the first punch (2 mm) followed by the second punch (4 mm) 3 days later and before the first treatment administration. Two on-treatment skin biopsies will also be collected in Cycle 1, with the first punch (2 mm) on Day 5 and the second punch (4 mm) on Day 8 before drug administration.
- dd **AEs.** All SAEs occurring after informed consent date and until the first study drug administration will be collected following SAE reporting guidelines and will be recorded in the AE eCRF (Section 8.1.1).
- ee **AEs.** All SAEs/AESIs occurring after 28 days after the last study drug administration or patient EOS should be reported to the Sponsor if the Investigator suspects a causal relationship to the study treatment (Section 8.1.1).

ADA, anti-drug antibody; AE, adverse event; AESI, adverse event of special interest; CRS, cytokine release syndrome; CT, computed tomography; D, Day; ECG, electrocardiogram; ECOG, Eastern Cooperative Oncology Group; eCRF, electronic case report form; EOS, end of study; FU, follow-up; HBsAg, hepatitis B surface antigen; HBV, hepatitis B virus; HCV, hepatitis C virus; Ig, immunoglobulin; IRR, infusion related reaction; MRI, magnetic resonance imaging; MUGA, multi-gated acquisition scan; PCR, polymerase chain reaction; PD, progressive disease; PK, pharmacokinetic(s); PS, performance status; RECIST, Response Evaluation Criteria in Solid Tumors; RNA, ribonucleic acid; SAE, serious adverse event; TSH, thyroid-stimulating hormone.

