### 5.2.3 Initiation of a New Study Drug Administration

Study drug must only be administered to eligible patients. Patient suitability for receiving study treatment is decided before each administration by the Investigator, based on protocol eligibility criteria for the initial administration (Section 4) and on scheduled pre-infusion safety assessments for subsequent administrations (Sections 7.4.11).

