### 5.2.5 Dose-Limiting Toxicities

DLT evaluation and a recommendation regarding dose-escalation steps will be made by the DERC (Section 8.5), after consideration of all available safety information.

A DLT is defined as an AE or abnormal laboratory result meeting any of the criteria below, that is assessed by the Investigator as related to study treatment, and that occurs within the DLT evaluation period, including death (Section 5.2.6). Severity of all AEs will be assessed according to NCI CTCAE v5.0.

- Any  $\geq$  Grade 3 study drug-related non-hematologic AE, including the following abnormal laboratory results: Hepatic laboratory parameters potentially fulfilling Hy's Law criteria: AST or ALT  $\geq 3 \times$  ULN and concomitant total bilirubin  $\geq 2 \times$  ULN
- Any Grade 4 study drug-related hematologic AE or abnormal laboratory result (hematologic or non-hematologic)
- Grade 3 neutropenia lasting  $> 7$  days despite adequate standard-of-care medication
- Grade 3 or 4 febrile neutropenia (fever  $\geq 38.5$  °C)
- Grade 3 anemia that cannot be adequately treated by blood transfusions
- Inability to administer the next dose due to a drug-related AE or delayed administration of the next dose due to a drug-related AE and/or abnormal laboratory result lasting  $> 14$  days despite adequate medication
- Any other AE/abnormal laboratory result which, in the view of the Investigator and/or Sponsor, is deemed clinically significant and considered a DLT

Note that the following AEs/abnormal laboratory results, some of which are expected with the study treatment, will not be considered a DLT:

- Any transient Grade 3 or 4 abnormal laboratory results without any related clinical symptoms and lasting  $< 72$  h
- Grade 3 events that have not been optimally treated with standard-of-care medication, lasting  $< 7$  days
- Grade 4 amylase or lipase not associated with symptoms or clinical manifestations or radiologic signs of pancreatitis

- Grade  $\geq 3$  lymphocytopenia not associated with symptoms or clinical manifestations
- Grade 3 hypertension resolving within 48 h
- Grade 3 IRR resolving under adequate treatment (first event only)
- Grade 3 fatigue lasting  $\leq 14$  days

An AE considered by the Investigator to be disease-related should not be considered a DLT.

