## 5.2.6 Dose-Limiting Toxicity Evaluability

The evaluability rules for DLT assessment apply to dose-escalation cohorts only.

The DLT evaluation period is defined as the 4-week period after first study drug administration.

Patients evaluable for DLT must either a) receive at least 2 administrations of MP0317 at q3w dosing schedule or 3 administrations at q1w dosing schedule at the assigned dose level and be observed until pre-dose of Cycle 2 Day 8 or b) experience a DLT as defined in Section 5.2.5 during the DLT evaluation period.

A patient will not be considered as DLT evaluable and may be replaced if they experience any of the following events during the DLT evaluation period:

- Received an MP0317 dose which is less than 90% or more than 110% of the planned infusion dose.
- Discontinued from treatment due to AE or death unrelated to study treatment, withdrawal of consent, lost to follow-up or Investigator decision (unrelated to study treatment).

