|         | Day 1, EOI                                                                   |                      | X (± 15 min)                   |                  |                                     |                             |                                            |              |                             |                                                     |                  |                           |
|         | Day 1, EOI + 15 min                                                          |                      |                                |                  |                                     |                             |                                            | X (± 10 min) |                             |                                                     |                  |                           |
|         | Day 1, EOI + 4 h                                                             |                      | X (± 15 min)                   |                  |                                     |                             |                                            | X (± 15 min) |                             | X (± 15 min)                                        |                  |                           |
|         |                                                                              |                      |                                |                  |                                     |                             |                                            |              |                             |                                                     |                  |                           |
|         | Day 8, before start of infusion                                              | X                    | X (max -2 h)                   |                  |                                     | X                           |                                            | X (max -2 h) | X (max -2 h)                | X (max -2 h)                                        |                  | X (± 3 days) d |

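### On q1w, no safety laboratory panel is scheduled between the fourth infusion and the end of the DLT window, so late asymptomatic laboratory DLTs may be under-counted

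*Protocol*

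**What the plan says.** Section 5.2.6 sets the window: "The DLT evaluation period is defined as the 4-week period after first study drug administration". To be evaluable without a DLT, a q1w patient must receive "3 administrations at q1w dosing schedule at the assigned dose level and be observed until pre-dose of Cycle 2 Day 8".

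Section 5.2.5 makes laboratory results DLT criteria in their own right. They include transaminase and bilirubin values potentially meeting Hy's Law, and "Any Grade 4 study drug-related hematologic AE or abnormal laboratory result (hematologic or non-hematologic"). Some results are exempt, among them "Any transient Grade 3 or 4 abnormal laboratory results without any related clinical symptoms and lasting" less than 72 h.

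For q1w, Table 14 places the Cycle 2 safety laboratories on Days 1 and 15 only, and footnote q gives the rule: "Laboratory safety assessments from cycle 2 onwards take place before every second drug administration". In Table 16, the row "Day 8, before start of infusion" marks physical examination, vital signs, pregnancy test, PK, ADA, blood biomarkers and tumor biopsy. Its local safety laboratory cell is empty. For q3w, Tables 7 and 9 schedule the safety panel at Cycle 2 Day 8.

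**The concern.** The grid, the footnote and the detailed table agree, so the empty cell is neither a slip nor a fault of text extraction. The difficulty is where the every-second-administration rule begins. It starts at Cycle 2 Day 1, but the DLT window runs one week longer. The schedule with more infusions in the window thus has fewer laboratory looks, and the missing look is the only one that would follow the fourth infusion.

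Incidence of DLTs is a primary endpoint (Section 2.2.1), and DLTs in the dose-determining set are the data that update the BLRM (Section 9.4.1.1). Section 1.1 names hepatotoxicity as a dose-limiting effect of earlier CD40 agonists, and Section 1.3.3 says the four weeks are meant to capture delayed as well as acute immune toxicity. A symptom-free liver or blood-count change is what a scheduled panel finds and what history and examination can miss. Any error has one sign: an unseen event lowers the q1w DLT count and cannot raise it.

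**Working it through.** **1. Day count.** With 21-day cycles (Section 5.2.1), study day = 21 × (cycle − 1) + cycle day. Cycle 2 Day 1 is 21 + 1 = 22, Cycle 2 Day 8 is 21 + 8 = 29, and Cycle 2 Day 15 is 21 + 15 = 36. Day 29 is 28 days after Day 1, which agrees with the stated 4 weeks.

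**2. Infusions and scheduled panels** (Tables 7 and 9 for q3w, Tables 14 to 16 for q1w):

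| | Day 1 | Day 8 | Day 15 | Day 22 | Day 29 | Day 36 |
|---|---|---|---|---|---|---|
| q1w infusion | 1 | 2 | 3 | 4 | 5 | 6 |
| q1w panel | yes | yes | yes | yes, pre-dose | none | yes |
| q3w infusion | 1 | – | – | 2 | – | – |
| q3w panel | yes | yes | yes | yes, pre-dose | yes | yes |

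**3. Uncovered part of the window.** On q1w it is 29 − 22 = 7 days, and 7/28 = 25%. The Day 22 sample may be drawn up to 48 h early, so the gap can reach 9 days (9/28 = 32%). The Day 36 sample may also be drawn 48 h early, on Day 34, still 5 days after the window closes. On q3w the gap is 0 days on schedule. If the second q3w dose uses its 2-day allowance (Table 5), the Cycle 2 Day 8 sample moves to Day 31, so q3w coverage sits on the window's edge.

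**4. Can one event matter?** The q1w prior is left to the SAP (Section 9.4.1.4), so the q3w model is used as a stand-in:
- Model: logit p(d) = log α + β log(d / 1 mg/kg).
- Prior (Table 23): log α ~ N(−2.685, 2²), log β ~ N(−0.594, 0.5²), correlation 0.
- Data: 0/3 at 0.03, 0.10 and 0.30 mg/kg, then r/3 at 1.00 mg/kg.
- Limit (Section 9.4.1.1): a dose with more than a 25% chance of excessive toxicity is not considered.

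| DLTs at 1.00 mg/kg | P(overdose) at 3.00, Table 30 | Recomputed by grid integration | Escalation to 3.00 |
|---|---|---|---|
| 0/3 | 0.055 | 0.053 | allowed |
| 1/3 | 0.306 | 0.303 | not allowed |

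Table 30 is reproduced, and one unseen event in three patients reverses the recommendation here. It does not do so everywhere. In Setting 2, one DLT in three at 0.10 or 0.30 mg/kg still allows escalation (0.193 and 0.241). In Setting 4a, one in six at 1.00 mg/kg also does (0.180).

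**5. Size, by assumption only.** Let s be the share of the DLT hazard that is laboratory-only and f the fraction of that hazard falling in the last week, with nothing found by unscheduled tests. The recorded rate is 1 − (1 − p)^(1 − s·f). For p = 0.33:

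| s | f | Recorded rate | P(at least 1 DLT in 3) |
|---|---|---|---|
| none missed | – | 0.33 | 1 − 0.67³ = 0.70 |
| 0.25 | 0.25 | 0.31 | 1 − 0.67^2.8125 = 0.68 |
| 0.5 | 0.5 | 0.26 | 1 − 0.67^2.25 = 0.59 |
| 1.0 | 0.5 | 0.18 | 1 − 0.67^1.5 = 0.45 |

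The protocol gives no value for s or f. The table shows a range, not an estimate.

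**The case against.** Several stronger readings are tempting, and the protocol does not support them.

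- **Late laboratory DLTs cannot be seen.** Unscheduled assessments are provided for when clinically indicated (Section 7.3.1), and Section 11.2.1 calls for extra safety assessments as needed. AEs are monitored continuously, and examination and vital signs are scheduled at q1w Cycle 2 Day 8. Clinically significant abnormal values are repeated (Section 7.4.11), so an abnormality found on Day 22 is followed. What remains is a new, symptom-free abnormality after Day 22 that lasts at least 72 h and is not otherwise exempt.
- **Every laboratory criterion is affected.** Grade 3 neutropenia must last more than 7 days. An onset after the Day 22 infusion cannot meet that by pre-dose on Day 29.
- **Evaluable patients are unmonitored after a required dose.** Evaluability needs three q1w infusions, and each of these is followed by a panel (Days 8, 15, 22). The gap concerns the fourth, which is inside the window but not required.
- **The Day 36 value always comes too late for the decision.** The first two patients start at least 7 days apart (Section 5.2.8), so on schedule the first patient's Day 36 is no later than the second's Day 29. No such spacing applies to later patients. In any case, an abnormality first found on Day 34 to 36 cannot be dated to the window.
- **q1w will look safer than q3w.** Decision rules and MTDs are independent by schedule (Sections 5.2.7.1 and 5.2.7.3), and no comparison is planned. The DERC also weighs PK, pharmacodynamic and other safety data (Section 8.5).
- **Section 5.2.3 contradicts footnote q.** It says "Patient suitability for receiving study treatment is decided before each administration by the Investigator", but goes on to base later administrations on the scheduled pre-infusion assessments. Section 7.4.11 ties laboratories to the time points in the schedule. The passages are compatible.

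These points narrow the matter but do not remove it. None of them puts a scheduled laboratory look between the fourth infusion and the close of the window.

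**Conclusion.** The point stands as a limited ascertainment gap that should be fixed. It is a consistent design choice, not an internal contradiction. On q1w the last scheduled safety panel in the DLT window precedes the fourth infusion, and at least 7 of 28 days (25%) have no scheduled laboratory look, against none on q3w when dosing is on time. New asymptomatic laboratory DLTs with onset in that week, such as potential Hy's Law values or Grade 4 results lasting at least 72 h, may be under-ascertained. Any resulting bias in the q1w DLT count is downward.

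The day count and the direction rest on the protocol alone. The size does not: it depends on how many DLTs are laboratory-only, how late they arise and how many unscheduled tests catch. That one event can turn a decision is shown only for cohorts of three, at certain doses, with the q3w prior standing in for the unseen q1w prior.

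**What to change.** In Table 14 (Cycle 2) and in the Cycle 2 Day 8 pre-dose row of Table 16, mark the local safety laboratory panel for q1w dose-escalation cohorts. Amend footnote q so that the every-second-administration rule applies only after the DLT evaluation period. The sample is best drawn at the visit, with the PK and ADA samples. If the usual 48 h allowance is used instead, up to 2 days of the window stay uncovered.

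The cost is one additional local panel per q1w escalation patient. That is 12 to 18 panels on the Section 9.1 numbers, at a visit where blood is already drawn. The uncovered part of the q1w window falls from 7 days to 0 for samples taken at the visit, matching q3w.
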